#### 5.4 THE INTERVENTION

Immediately after randomization, participants in the intervention group will be directed to the *i-HPV website* and will receive information about HPV and the HPV vaccine. This *website* will be developed in a *mobile version* , but it will also be accessible from *desktops* . The content will be produced based on the theoretical basis of the TMP and will later be revised, based on improvements identified after conducting a focus group with PLWHA and/or workers from institutions aimed at assisting this key population. For this group, the *website* will be developed in four sequential sections, with simple, accessible language and a design that follows the trend of intuitive scrolling on screens, typical of *smartphones* . The four sections are:

- i. Learn more about HPV : This session included information on HPV prevalence, transmission, HPV-related diseases, and increased risk for PLWHA. **Perceived severity** and **perceived vulnerability were used as theoretical constructs in this section** .
- ii. Learn about the HPV vaccine : This session provides information about the HPV vaccine, its effectiveness, recommendations for key populations, and testimonials focusing on the reasons why people living with HIV should get vaccinated. The theoretical construct used is the **effectiveness of the response** , in this case, of vaccination.
- iii. Frequently Asked Questions : This is a question and answer session used to provide information related to barriers and concerns about HPV and the HPV vaccine obtained from previous research and the focus group conducted prior to the intervention. Here, the **response cost variable will be explored** .

- iv. Get vaccinated : This session provides information on vaccination sites and the documents required to obtain the vaccine. At this stage, the construct of **self-efficacy** is explored, as the participant will be led to evaluate their intention to get vaccinated within a certain period of time

## 5.5 THE CONTROL GROUP

Participants in the control group will be redirected to the MS-HPV *website immediately after randomization. This website will also present information about HPV and the HPV vaccine, but it will be obtained from the website <http://saude.gov.br/saude-de-az/hpv>* , which is dedicated to informing the general population about HPV and is maintained by the MS. To avoid major disparities in content between the groups, information from this website will be cut to a new page developed for the project. The content will be reproduced in an attempt to maintain correspondence with the topics covered on the intervention group page. Thus, the following sections will be reproduced: “What is HPV”, “Signs and Symptoms”, “Prevention” and “Questions and Answers”. This version will include the same content from the “Get Vaccinated” section, presented to the intervention group.

## 5.6 DATA COLLECTION

In both iHPV and MS-HPV, as soon as the participant starts browsing the “Get vaccinated” section, they will be asked about their intention to get vaccinated in the next three months. Their response will allow us to capture the primary outcome of the intervention. It also serves as a trigger for the start of the self-reported data collection phase.

It will be done in two ways: automatic collection via browsing data and questionnaire. In automatic collection, the origin and time of access to the pages will be recorded. Through questionnaires, sociodemographic data , intention to get vaccinated, evaluation of the intervention, and reasons for not getting vaccinated will be collected. All data will be collected electronically and saved in a database with restricted access to researchers.

## 6. ANALYSIS PROPOSAL

### 6.1 VARIABLES

The variables and the objectives they will respond to are described below.

#### 6.1.1 Viability of invitations

It will be measured by the access rate in each dissemination strategy. The viability of physical invitations (VCF) will be measured by the ratio between the number of accesses to the P0 home page originated from posters and pamphlets (nP0PP) and the estimated number of services to PLWHA ( nA ) carried out at the service locations, during the recruitment period.

$$= \frac{\text{nP0PP}}{\text{nA}}$$

*online* invitations (VCO), the ideal situation would be to measure the number of accesses to P0 originated from *online posts* (nP0PO) in relation to the number of views of these same *posts* . This situation is not possible since the dissemination will be done via free advertisements and in accounts not managed by the project. Therefore, we will consider as the denominator the total number of followers, on the last day of recruitment, on the social media of the institutions listed in item 4.1.2 where the *posts* should be published ( nS ).

$$= \frac{\text{nP0PO}}{\text{nS}}$$

This way, it will be possible to compare strategies, evaluating their respective performance in recruiting participants.

#### 6.1.2 Acceptability

It will be expressed by the percentage of satisfied participants in the three dimensions of analysis:

- a) Information quality
- b) Website quality
- c) Usefulness of intervention

And by the indicators below:

- d) Abandonment rate: Ratio between the number of participants who enter and leave without any interaction and the total number of accesses to the page.
- e) Average dwell time, per page and per section

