## 6.2 DATA ANALYSIS METHODOLOGY

A descriptive analysis of the frequency distribution of the main outcome variables and other variables will be performed. Continuous variables will be expressed as mean  $\pm$  standard deviation with a 95% confidence interval (CI), and categorical variables will be expressed as frequencies and percentages. To assess the effects of the intervention on the intention to get vaccinated (effectiveness), the groups will initially be assessed for sample homogeneity in relation to demographic and health-related characteristics. Differences between the groups studied will be calculated using *Student's t-test*. for quantitative variables and, for categorical variables, the comparison between groups will be performed using the Chi-square test. The logistic regression model will be used to compare the study groups in all outcomes, adjusting for potential confounding variables . Statistical analyses will be performed using the *software* Stata 12. P-values <0.05 will be considered statistically significant.

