### 6.2.1 Primary outcome

Percentage of PLWHA intending to receive the HPV vaccine.

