### 6.2.2 Secondary outcome

Vaccination initiation rate (at least one dose of vaccine) among PLWHA and complete vaccination rate (three doses of vaccine).

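### The abandonment rate in Protocol section 6.1.2 divides people by page visits, so it falls as visits per participant rise even when the same share of participants leave

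*Protocol*

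**What the plan says.** Acceptability is part of the general objective (Protocol section 4.1) and is specific objective 4.2.2. Section 6.1.2 measures it by the percentage of satisfied participants in three dimensions and by two browsing indicators. Item d is the abandonment rate: "Ratio between the number of participants who enter and leave without any interaction and the total number of accesses to the page". Item e is "Average dwell time, per page and per section".

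Section 5.6 describes the source of the browsing data: "In automatic collection, the origin and time of access to the pages will be recorded". It does not say whether repeat accesses by one person are recognised, or whether an access is tied to that person's randomised record.

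Section 6.1.3, on effectiveness, uses a different kind of denominator: the participants randomised to each website (nP).

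Section 6.2 says of the analysis: "Differences between the groups studied will be calculated using *Student's t-test*. for quantitative variables", and then: "The logistic regression model will be used to compare the study groups in all outcomes, adjusting for potential confounding variables". The primary outcome in section 6.2.1 is "Percentage of PLWHA intending to receive the HPV vaccine". The secondary outcomes in section 6.2.2 are starting and completing vaccination. All three are yes/no for each person.

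**The concern.** A rate needs the same unit above and below the line. Here each person who leaves adds at most one to the numerator, while every page load by anyone adds one to the denominator. Return visits and reloads therefore enlarge only the denominator. The result is neither the proportion of participants who left nor the proportion of visits that ended without interaction.

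The two websites are built differently. The intervention site has four sequential scrolling sections (section 5.4), and the control site carries sections cut from the Ministry page plus the shared vaccination section (section 5.5). Equal revisit frequency cannot be taken for granted. A site that draws more return visits would show lower abandonment even if the same share of its participants left at once. A real difference in abandonment could also be hidden.

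This is not detail left for a later analysis plan. The protocol fixes both numerator and denominator, and an analysis plan that follows it would inherit the mismatch.

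**Working it through.** **Plan's own figure.** The protocol states no abandonment rate, access count or dwell time, so there is no figure to reproduce for this indicator. All access counts below are assumptions.

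**Notation.** N = participants sent to a website; p = true share who leave without interacting; m = mean accesses per participant (total accesses divided by N).

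**Step 1. The ratio as written.** The numerator is pN and the denominator is mN, so the ratio is pN / (mN) = p / m. It equals p only when m = 1.

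**Step 2. Illustration with p = 20%.** Column A applies p / m. In column B those who leave make one access each and the others make k each, so the ratio is p / (p + (1 − p)k).

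| Accesses (m in A, k in B) | A | B |
|---|---|---|
| 1 | 0.20/1 = 20.0% | 0.20/1.00 = 20.0% |
| 1.5 | 0.20/1.5 = 13.3% | 0.20/1.40 = 14.3% |
| 2 | 0.20/2 = 10.0% | 0.20/1.80 = 11.1% |
| 3 | 0.20/3 = 6.7% | 0.20/2.60 = 7.7% |

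**Step 3. Between websites.** With 20% abandonment on both sites, 1 access per person on one and 2 on the other, the formula shows 20% against 10% to 11%. Conversely, a true 30% at m = 3 and a true 20% at m = 2 both read 10% (0.30/3 and 0.20/2), which hides a 10-point difference.

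**Step 4. One unit in both terms.** Participants over participants gives pN / N = p, whatever m is. Accesses over accesses is a valid proportion of visits, but it still moves with revisit frequency: under column B, if every access by those who stay includes some interaction, it gives the same 14.3%, 11.1% and 7.7%. It mends the unit, not the dependence on browsing.

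**Step 5. Does dwell time share the fault?** Item e is a mean time and has no ratio of people to visits. To see whether skewed times would invalidate a t-test, log-normal times were simulated with 293 per arm (section 6.2.3), assumed log-scale SDs of 0.8, 1.0, 1.2 and 1.5, and 10,000 runs each. Type I error was 4.7%, 5.0%, 4.5% and 4.0% against a nominal 5%. For a shift of 0.2 log-SD, power was 31% to 55% on the raw scale and 67% to 69% on the log scale. Under these assumptions skew costs power, not validity.

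**Step 6. Sample size.** With 20% against 30%, two-sided 5%, 80% power and the pooled normal approximation: n = [1.96·√(2·0.25·0.75) + 0.8416·√(0.20·0.80 + 0.30·0.70)]² / 0.10² ≈ 293.2, or 294 when rounded up. Power at the stated 293 is 79.98%. The plan's figure holds and does not depend on the abandonment rate.

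**The case against.** The strongest reply is that item d describes a page-level web metric. Section 6.1.1 also works in accesses, and item d does not say which page is meant, so the authors may have intended visits in both terms. If so, a change of wording to accesses ending without interaction would be enough, and nP is not the only valid denominator. That stands, and the fix allows for it. It does not rescue the text, which counts participants in the numerator.

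A second reply is that the figures are hypothetical and that the mismatch is harmless if each person makes exactly one access. That is also true. But the protocol states no such rule, and the direction of the error does not depend on the figures chosen.

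A reader might infer more than the documents support:

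- *That dwell time is wrongly defined or its t-test invalid.* A mean time is a legitimate summary, and section 6.2 never names dwell time. Its t-test sentence follows one on baseline comparability and may refer to that. A log scale, medians or an inactivity cut-off are choices that an analysis plan commonly carries.
- *That the logistic model cannot be fitted as planned.* This would need dwell time to be one of the outcomes in "The logistic regression model will be used to compare the study groups in all outcomes". The outcomes named in sections 6.2.1 and 6.2.2 are all binary, so the wording is loose rather than unworkable.
- *That the abandonment rate is the plan's measure of missing primary data.* The protocol lists it only under acceptability. Effectiveness is divided by nP, and dropout is allowed for separately in section 6.2.3.

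**Conclusion.** The point holds for the abandonment rate alone. As defined, the rate mixes persons with visits and equals the per-participant rate divided by mean accesses per participant. It is understated whenever that mean exceeds one, and it can differ between the websites with no difference in abandonment. On assumed access counts, a true 20% reads 10% at 2 accesses per participant and 6.7% at 3. The direction follows from the definition; the size cannot be known from the protocol.

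The correction is worth making because the indicator serves a stated objective and the repair is cheap. It changes nothing in the primary outcome, the named secondary outcomes or the sample size. The reference to all outcomes in section 6.2 is a separate, minor matter of wording. No fault is established in the dwell-time indicator.

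**What to change.** In section 6.1.2, item d, use one unit in both terms and name the page or website meant. Preferably, define abandonment for each website as the number of unique randomised participants who leave without interacting, divided by the number randomised to that website (nP, as in section 6.1.3), and report it per arm.

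If accesses cannot be linked to participants, define it as accesses that end without interaction divided by total accesses, and label it a per-visit rate. It should then not be read as the share of participants lost, because it still varies with revisit frequency.

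In section 6.2, limit the logistic regression sentence to binary outcomes.

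The cost is mainly wording. The preferred definition also needs the access log to carry a study code that ties each access to a randomised record. Section 5.6 does not confirm this, and section 9 says the database will hold no identity information. A code without identity should be compatible with that, but the link has to be confirmed and, if absent, built before data collection.

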### 6.1.3 Effectiveness

The effectiveness of the intervention (E) will be obtained by the percentage of participants who declared their intention to get vaccinated. Measured by the ratio between the sum of the number of participants who declare that they will or intend to get vaccinated ( nV ) and the number of participants in the groups randomized to their respective *websites* ( nP ).

$$= \frac{\text{---}}{\text{---}} \times 100$$

## 6.2 DATA ANALYSIS METHODOLOGY

A descriptive analysis of the frequency distribution of the main outcome variables and other variables will be performed. Continuous variables will be expressed as mean  $\pm$  standard deviation with a 95% confidence interval (CI), and categorical variables will be expressed as frequencies and percentages. To assess the effects of the intervention on the intention to get vaccinated (effectiveness), the groups will initially be assessed for sample homogeneity in relation to demographic and health-related characteristics. Differences between the groups studied will be calculated using *Student's t-test*. for quantitative variables and, for categorical variables, the comparison between groups will be performed using the Chi-square test. The logistic regression model will be used to compare the study groups in all outcomes, adjusting for potential confounding variables . Statistical analyses will be performed using the *software* Stata 12. P-values <0.05 will be considered statistically significant.

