### 5.2 INCLUSION CRITERIA

- i. Living with HIV/ AIDS.
- ii. Age between 18 and 45 years.
- iii. Consent to participate in the study.

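### Adjustment covariates are collected only after exposure and after the primary-outcome question, so the homogeneity check and adjusted model cover a post-randomisation subset while section 6.1.3 counts everyone randomised

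*Protocol*

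**What the plan says.** The protocol fixes the following order.

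- **Exposure.** Section 5.4 sends the intervention arm to the i-HPV site: "Immediately after randomization, participants in the intervention group will be directed to the". Section 5.5 does the same for controls and the MS-HPV site. No covariate questionnaire is described before this step.
- **Primary outcome.** Section 5.6, for both sites (the period is in months): "as soon as the participant starts browsing the “Get vaccinated” section, they will be asked about their intention to get vaccinated in the next three". Of the answer it says: "It also serves as a trigger for the start of the self-reported data collection phase".
- **Covariates.** Section 5.6 says that by questionnaire "sociodemographic data , intention to get vaccinated, evaluation of the intervention, and reasons for not getting vaccinated will be collected". The automatic log holds only where an access came from and its timing.
- **Use of the covariates.** Section 6.2: "the groups will initially be assessed for sample homogeneity in relation to demographic and health-related characteristics". Later in the same section: "The logistic regression model will be used to compare the study groups in all outcomes, adjusting for potential confounding variables".
- **Denominator.** Section 6.1.3 divides the number who say they will or intend to be vaccinated by everyone allocated to each site: "and the number of participants in the groups randomized to their respective".

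Eligibility (sections 5.2 and 5.3) requires HIV status, "Age between 18 and 45 years" and no previous HPV vaccine dose. The protocol does not say that these answers are stored for analysis.

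**The concern.** A covariate used to compare or adjust randomised groups should be available for everyone randomised and recorded before the arms can diverge. Here the sociodemographic items exist only for people who stayed on their assigned site long enough, answered the outcome question and went on to the questionnaire. Each of these steps follows exposure to content that differs by arm.

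Two things are at stake. The homogeneity check would not describe the groups that randomisation formed. The adjusted odds ratio would refer to a different population from the percentage in section 6.1.3. The hypothesis in section 2 is that a shorter, more visual site works better than the ministry's content, and section 6.1.2 plans to measure abandonment. Different completion by arm is therefore a realistic possibility.

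Separately, section 6.2 promises a comparison of health characteristics for which section 5.6 names no source.

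**Working it through.** **1. The plan's own figures.** Inputs from section 6.2.3: 20% vs 30%, alpha 5% (taken as two-sided), power 80%, 293 evaluable per group, 836 to 650 enrolled for 30% to 10% dropout.

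n per group = [1.96·√(2·0.25·0.75) + 0.8416·√(0.2·0.8 + 0.3·0.7)]² / 0.10² = (1.2002 + 0.5119)² / 0.01 ≈ 293.1, so 294 after rounding up. Power at 293 is 79.98%. Enrolment: 586/0.70 = 837.1 against 836, and 586/0.90 = 651.1 against 650. The stated figures reproduce, and the sample size is not at fault.

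**2. Who has covariates.** The sections set side by side:

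| Quantity | Population |
|---|---|
| Percentage intending (6.1.3) | all randomised to each site |
| Homogeneity check on questionnaire data (6.2) | those who reached *Get vaccinated*, answered, and completed the items |
| Logistic model adjusted for questionnaire data (6.2) | the same subset, if incomplete records are dropped |

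**3. Size of the gap.** Assume that the planned dropouts are the people who do not reach the questionnaire.

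- 650 × 0.10 = 65 without covariates, 585 left.
- 836 × 0.30 = 250.8, about 251 without covariates, 585 left.

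People who answer the intention question and then abandon the questionnaire would come on top. The protocol gives no figure for them.

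**4. What selective loss could do.** This is an illustration, and none of its assumptions is in the protocol: no true effect; 20% of each arm would intend; 90% of controls complete regardless of intention; intervention intenders also complete at 90%; all excess loss in the intervention arm falls on non-intenders; the covariates do not explain the loss.

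| Completion, control vs intervention | Intention among completers | Spurious difference | Rejection at nominal 5% (650 to 836 enrolled) |
|---|---|---|---|
| 90% vs 80% | 20% vs 0.20·0.90/0.80 = 22.5% | +2.5 points | 11% to 13% |
| 90% vs 70% | 20% vs 0.20·0.90/0.70 = 25.7% | +5.7 points | 34% to 42% |

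Rejection = Φ((d − 1.96·se0)/se1) + Φ((−d − 1.96·se0)/se1), with se0 pooled and se1 unpooled. For 650 enrolled and 90% vs 80%: group sizes 292.5 and 260, d = 0.025, se0 = 0.0348, se1 = 0.0349, giving 0.108 + 0.004 = 0.111.

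Over all randomised, as in section 6.1.3, both scenarios give 0.20 × 0.90 = 18% in each arm, so no difference. With equal, non-selective loss (80% in both arms), the completers' comparison also shows no bias and 5% rejection.

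**The case against.** The strongest reply has four parts.

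- **The same people mostly lack the outcome too.** Someone who never reaches *Get vaccinated* gives no intention answer either, so the 65 to 251 are not shown to be lost because of covariate timing. This stands as a limit on the numbers. It does not remove the mismatch: section 6.1.3 keeps these people in the denominator, in effect as not intending, and a complete-case adjusted model would not.
- **Some covariates may exist for everyone.** Age must be known for eligibility, and the source of access is logged. That is possible, but the protocol does not say that age is kept, and the other sociodemographic items come from the later questionnaire.
- **A website does not change fixed traits.** This is correct. The harm is selective availability, not altered values.
- **An analysis plan may deal with missing covariates.** It may, and the complete-case model is an assumption about handling that is not shown. An analysis plan cannot recover items that were never collected.

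A reader might also infer more than the text supports:

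- *That the homogeneity check selects the adjustment variables.* Section 6.2 states both steps and does not link them. Naming the covariates may be left to the analysis plan.
- *That the primary outcome is tested twice, by chi-square and by logistic regression.* The chi-square sentence follows directly on the homogeneity sentence and may describe only that check. Test order may also sit in the analysis plan.
- *That logistic regression is prescribed for dwell time.* Section 6.1.2 lists dwell time as an acceptability indicator. The outcomes named in sections 6.2.1 and 6.2.2 are all yes/no.
- *That the question comes last on both sites.* Section 5.4 supports this for the intervention site. Section 5.5 does not give the section's position on the control site.

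**Conclusion.** The point holds for the order of data collection. Sections 5.4 to 5.6 make the sociodemographic data available only after exposure and after the primary-outcome answer. The homogeneity check and any adjusted model in section 6.2 that uses them therefore rest on a post-randomisation subset, in conflict with the all-randomised denominator of section 6.1.3. The health characteristics in section 6.2 have no listed source in section 5.6.

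The gap is about 65 of 650 to 251 of 836 participants, on two assumptions: that the planned dropouts are those who do not reach the questionnaire, and that incomplete records are dropped from the model. The protocol gives no loss by arm, so the amount and direction of any bias are unknown. The illustration shows only what strongly selective loss could do.

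A reader might infer that the primary percentage itself is biased by this. It is not: the unadjusted figure in section 6.1.3 does not depend on the covariates.

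**What to change.** 1. Move the sociodemographic and health items meant for adjustment to the consent and eligibility form, completed before randomisation, and name the health items in section 5.6. Keep the evaluation of the site and the reasons for not being vaccinated where they are.
2. In section 6.2, present these characteristics descriptively by arm for all randomised participants.
3. Fit the adjusted logistic model for intention to all randomised participants, using only covariates recorded before randomisation (for example age, sex and recruitment source). Apply the section 6.1.3 rule, so that a participant without an intention answer stays in the denominator as not intending.

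The cost is a reordered web form and a few lines of text, if done before recruitment opens. Afterwards the missing covariates cannot be recovered. A longer entry form may turn some visitors away and slow recruitment, but they leave before allocation and so cannot bias the comparison.

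The all-randomised denominator that section 6.1.3 already uses has a price in power. If 20% vs 30% applies to those who answer, the rates over all randomised become 14% vs 21% (836 enrolled, power 76.0%) or 18% vs 27% (650 enrolled, 78.6%), against 79.9% among completers. Moving the form does not cause this.
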